## School randomisation

Schools will be stratified based on Pupil Premium (proxy for socioeconomic status, below/above the county-specific median; for information: https://www.gov.uk/guidance/pupil-premium-information-for-schools-and-alternative-provision-settings) and county (ie, Cambridgeshire or Essex). Randomisation lists for each stratum will be prepared by a statistician, using Stata (ref: StataCorp. 2015. Stata Statistical Software: Release 14. College Station, Texas, USA: StataCorp), after baseline measurements are completed to ensure schools and participants are unaware of their group allocation at baseline. Eight schools will be randomised to deliver the GoActive intervention and eight to a no-treatment control condition. For measurements after randomisation, it will not be possible to blind participants to randomised allocation as the intervention schools will have received the GoActive intervention.

Measurement staff will be blinded to intervention condition throughout the study as they will be trained and work separately from those involved in intervention delivery. Process evaluation with measurement staff will examine the success of blinding.

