## Analyses

### Sample size

We aim to detect a 5 min difference in change in MVPA per day at 10-month follow-up, as observed in the pilot study.^26^ A 5 min increase is relevant at population level as it would increase the proportion of adolescents meeting the guidelines of 60 min of MVPA per day from 43% to 50% (based on baseline pilot data), with significant impact on population health.^2^ To estimate the required sample size, the following parameters have been used: power=85%, significance level=5%, SD=17.8 (observed in the GoActive pilot),^26^ intraclass correlation coefficient=0.034 (observed in SPEEDY-3, n=57 schools),^43^ correlation between baseline and follow-up MVPA=0.59 (observed in GoActive pilot, to account for adjustment for baseline MVPA)^26^ and average cluster size=100. Based on these parameters, we estimate n=1310 participants will be required for the primary effectiveness analysis. To account for potential school dropout and an estimated loss-to-follow-up of 30%–40%, we aim to recruit 16 schools with 150 participants (total n=2400; average recruitment per school in pilot=154).^26^ Should a school have >150 students in year 9, we will include all those who assent to measurement.

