### Outcome analyses

The primary efficacy outcome, MVPA, will be compared between intervention and control groups using analysis of covariance, with adjustment for baseline MVPA; robust SEs will be calculated to allow for the non-independence of individuals within each school. Where baseline values of MVPA are missing, the missing indicator method will be used to enable these participants to be included in the analysis.^57^ An estimate of the intervention effect, 95% CI and p value will be calculated. A similar method will be used for the secondary efficacy outcomes. School-level data will also enable analysis of key differences between those participating in the evaluation and the wider school population; for example, patterns of non-response by demographic variables will be explored. Subgroup analyses by prespecified moderators (sex, socioeconomic status, ethnicity, baseline activity level, weight status) will be performed for the primary outcome only. The interaction between randomised group and each moderator will be tested, and if the p value is <0.05, the intervention effect (difference between intervention and control, and 95% CI) will be estimated within each subgroup. The effect on potential mediating variables will initially be assessed as described above. We will subsequently conduct formal mediation analyses using the product of coefficient method^58^ to assess the underlying causal pathways of the intervention.

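### With 16 schools, plain cluster-robust standard errors in a model without the stratification factors leave the primary test uncalibrated, and the error can run either way

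*Protocol article*

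**What the plan says.** Protocol article, Outcome analyses: MVPA is compared between arms by analysis of covariance with baseline MVPA as the only covariate named. For clustering, "robust SEs will be calculated to allow for the non-independence of individuals within each school". From that model, "An estimate of the intervention effect, 95% CI and p value will be calculated". Secondary outcomes are to be handled in a similar way, and the mediators are first assessed by the same approach.

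Protocol article, School randomisation: "Eight schools will be randomised to deliver the GoActive intervention and eight to a no-treatment control condition". Allocation is stratified by county and by Pupil Premium (below or above the county median).

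Protocol article, Sample size: "we aim to recruit 16 schools with 150 participants". The planning values are "power=85%, significance level=5%, SD=17.8", "intraclass correlation coefficient=0.034", "correlation between baseline and follow-up MVPA=0.59" and an average of 100 pupils analysed per school.

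The article mentions no small-sample correction, between-school degrees of freedom, school-level analysis or use of the strata in the model.

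**The concern.** The robust (sandwich) variance is justified as the number of clusters grows. Adding pupils within schools does not help. With eight schools per arm, each school's residual is measured from an arm mean that the school itself helped to set, so the variance comes out too small unless it is corrected. That pushes the type I error above 5% and narrows the interval.

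A second feature pushes the other way. Stratified allocation balances county and Pupil Premium between arms. If these predict MVPA, the treatment contrast varies less than a model without them supposes, and its standard error is too large.

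The two errors have different causes, and nothing makes them cancel. At stake are the p value and CI for the main claim of the trial, and those for the secondary outcomes analysed in the same way.

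**Working it through.** **Inputs.** From the article: 16 schools (8 and 8), 100 analysed per school, SD 17.8, ICC 0.034, correlation 0.59, difference 5 min, 5% level (taken as two-sided, to match the 95% CI), power 85%. Assumed here: the spread of school sizes (coefficient of variation, CV), the share of between-school variance that the strata explain, and that the ICC applies on the baseline-adjusted scale.

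**1. The plan's own figure.** Residual variance = 17.8² × (1 − 0.59²) = 206.5. Per arm, n = 2 × 206.5 × (1.960 + 1.036)² / 5² = 148.4. Design effect = 1 + 99 × 0.034 = 4.366. Total = 2 × 148.4 × 4.366 = 1,295, or 2 × 150 × 4.366 = 1,310 with 150 per arm. The stated 1,310 is reproduced. It uses normal quantiles and makes no allowance for few clusters.

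**2. Size of the robust SE: equal schools, strata not prognostic.** The uncorrected variance averages 14/16 = 7/8 of the truth, an SE ratio of √(14/16) = 0.935. With the common factor G/(G−1) = 16/15, the SE ratio is √(14/15) = 0.966. The correct reference is t on 14 df, with critical value 2.145.

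| Version | Type I error | CI width against t(14) |
|---|---|---|
| Uncorrected, normal | P(\|t14\| > 1.96 × 0.935) = 8.8% | 1.96 × 0.935 / 2.145 = 85% |
| 16/15, normal | P(\|t14\| > 1.96 × 0.966) = 7.9% | 88% |
| 16/15, t(15) | P(\|t14\| > 2.131 × 0.966) = 5.9% | 96% |

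**3. Simulation with baseline adjustment, strata not prognostic.** Type I error for the three versions, in the same order:
- equal schools: 9.1%, 8.2%, 6.1%
- size CV 0.3: 9.5%, 8.5%, 6.3%
- size CV 0.5: 11.0%, 10.2%, 7.5%
- 14 schools remaining, CV 0.3: 10.6%, 9.2%, 6.5%

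**4. Prognostic strata left out of the model.** Take four strata of four schools, two per arm in each, and let the strata explain a share s of the between-school variance. On a scale with total variance 1, the variance of a school mean within stratum is v = 0.034(1 − s) + 0.966/100. The uncorrected robust variance then averages 7/8 + 0.034s/v of the truth:
- s = 10%: v = 0.0403, ratio 0.875 + 0.084 = 0.96
- s = 20%: v = 0.0369, ratio 0.875 + 0.184 = 1.06
- s = 30%: v = 0.0335, ratio 0.875 + 0.305 = 1.18

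The bias changes sign within this range. Simulated type I error with 16/15 and t(15) at equal sizes is 4.7%, 3.7% and 3.1%. At size CV 0.3 it is 5.8%, 4.5% and 3.5%. Uncorrected with a normal reference, equal sizes, it is about 7.0%, 6.1% and 5.4%.

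**5. Strata added but plain robust SEs kept.** With the four strata in the model (size CV 0 or 0.3), type I error is 14% to 15% uncorrected with a normal reference, and 10% to 11% with 16/15 and t(15).

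**6. Power after correction.** SE = √(2 × 206.5 × 4.366 / 800) = 1.50, and 5/1.50 = 3.33. Power is 91.5% with a normal reference, 87.2% on t(14), and 85.7% on 11 df if all four strata are fitted with no gain in precision.

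**The case against.** The strongest objection is the offset in step 4. With stratified allocation and no strata in the model, the test may be near nominal or conservative. This stands. A reader might infer that the test must exceed 5% and that the interval must be too narrow. The documents do not support that, because they do not say how strongly county and Pupil Premium predict MVPA.

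A second objection is that common software applies the 16/15 factor and t(15) by default, which leaves about one point of excess. That is a fair account of the mildest case with equal schools. However, the article names Stata only for the randomisation lists and gives no reference distribution, so the mild case cannot be assumed. Unequal school sizes also raise it to 6.3% to 7.5% when strata are not prognostic.

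A third is that the finite-sample factor and degrees of freedom belong in a statistical analysis plan that is not shown. This stands in part. A bias-corrected robust SE would be compatible with the protocol wording, and a separate plan may specify one. But the article does fix a method for clustering and a covariate set, and carried out as written with 16 schools they are not calibrated.

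The figures of 10% to 15% in step 5 describe a model that the article does not state. They are a warning about a partial fix, not a measure of the present plan.

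**Conclusion.** The point holds as a lack of calibration, not as a certain inflation. If the strata are not prognostic, type I error is about 6% with 16/15 and t(15), and about 8% to 9% with a normal reference. It is higher with unequal schools, and the interval is 96% to 85% of the correct t(14) width. If the strata explain 10% to 30% of between-school variance, the error with t(15) at equal sizes is about 5% to 3%. The first set rests on the article's planning values and, for unequal schools, on assumed size variation. The second also rests on the assumed share explained by strata. The sample size calculation reproduces and is not in dispute.

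**What to change.** State in Outcome analyses that the stratification factors (county and Pupil Premium) enter the model, and that inference uses a method valid with few clusters. Any of these would do:
- bias-corrected (CR2) robust SEs with Satterthwaite degrees of freedom
- a linear mixed model with a random school intercept and Kenward-Roger or Satterthwaite degrees of freedom
- a baseline-adjusted school-level analysis, with t on the number of schools minus the number of school-level parameters

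Apply the same choice to the secondary outcomes. The two changes belong together: adding the strata while keeping plain robust SEs makes the inflation worse.

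The change is a sentence or two and needs no extra schools or data. The interval widens by about 4% compared with 16/15 and t(15) (1/0.960 = 1.04). It widens by 13% to 17% compared with a normal reference (1/0.883 = 1.13, 1/0.855 = 1.17). Both are before any precision gained from the strata. With 16 schools of 100, power for 5 min is about 87% on t(14), above the planned 85%. If only 14 schools of 100 remained, it would be about 82% on 12 df, against 88% with a normal reference.

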### Objectives

The primary aim of this study is to assess the 10-month effectiveness of the GoActive intervention to increase average daily objectively measured MVPA among 13–14-year-old adolescents. We will also assess the effect of GoActive immediately postintervention, and on the following secondary outcomes: (1) objectively assessed activity intensities during school time, weekday evenings and weekends; (2) student-reported physical activity participation, self-efficacy, peer support, social networks, self-esteem, friendship quality (proposed mediators) and well-being, and school-level attendance and academic performance; and (3) body composition (body fat percentage and body mass index (BMI) z-score). We will investigate potential moderation of intervention effects by sex, socioeconomic status, ethnicity, baseline activity level and weight status, and potential mechanisms of effect by proposed mediators using a mixed-methods approach. Further, we will assess short-term (within-trial) and potential long-term cost-effectiveness of the GoActive intervention and will conduct a comprehensive process evaluation including questionnaires, focus groups, and individual interviews (with participants, mentors, teachers, and intervention facilitators), data from intervention logs and website analytics.

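### Subgroup effects and their CIs are estimated only where the interaction gives p<0.05, so those shown are selected and, for modest interactions, inflated

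*Protocol article*

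**What the plan says.** The Objectives section of the protocol article states: "We will investigate potential moderation of intervention effects by sex, socioeconomic status, ethnicity, baseline activity level and weight status".

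The Outcome analyses section limits this work to MVPA: "Subgroup analyses by prespecified moderators (sex, socioeconomic status, ethnicity, baseline activity level, weight status) will be performed for the primary outcome only". Every moderator is tested: "The interaction between randomised group and each moderator will be tested". The next step is conditional: "if the p value is <0.05, the intervention effect (difference between intervention and control, and 95% CI) will be estimated within each subgroup".

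The Sample size section concerns the main effect only: "We aim to detect a 5 min difference in change in MVPA per day at 10-month follow-up". It gives no interaction size, subgroup share or power for an interaction. The article does not say that non-significant interaction tests will go unreported. Nor does it commit to giving interaction estimates with CIs for them.

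**The concern.** The rule puts a significance threshold between the data and the subgroup estimates, with two consequences.

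- **Selection.** Subgroup effects appear only when the observed interaction is large relative to its standard error. If the true interaction is modest, the estimates that pass are on average further apart than the truth. If there is no interaction, those that pass arise by chance.
- **Loss of information.** When p is 0.05 or more, no subgroup effect or CI is planned. The reader cannot tell whether the effect is much the same in both groups or the comparison was too imprecise to say.

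This matters because the Background presents GoActive as an intervention for all groups, in contrast to earlier programmes aimed at subgroups. For that claim, the effect with its CI in each sex, in socioeconomic groups and in less active students is useful whether or not the interaction is significant.

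**Working it through.** **1. Inputs from the Sample size section.** Target difference 5 min; "power=85%, significance level=5%, SD=17.8 (observed in the GoActive pilot"; "intraclass correlation coefficient=0.034 (observed in SPEEDY-3, n=57 schools"; "correlation between baseline and follow-up MVPA=0.59"; average cluster size 100; loss to follow-up 30%–40% of 2400 recruited. Two-sided testing is assumed.

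**2. Reproducing the plan's own figure.**
- Variance after baseline adjustment: 17.8² × (1 − 0.59²) = 316.84 × 0.6519 = 206.5 (SD 14.37).
- n per arm before clustering: 2 × 206.5 × (1.960 + 1.036)² / 5² = 148.4.
- Design effect: 1 + 99 × 0.034 = 4.366.
- Total: 2 × 148.4 × 4.366 ≈ 1295, or 1301 if n per arm is first rounded up to 149.

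The article states 1310, within about 1% of this. The figure reproduces, and the same variance inputs can be used for the interaction.

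**3. Standard error of an interaction.** Take a student-level moderator split 50:50 within schools (assumed). School effects shared by both categories largely cancel, leaving a fraction 1 − 0.034 = 0.966 of the variance. The interaction contrasts four cells of N/4:

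SE = √[4 × 206.5 × 0.966 / (N/4)]

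Three values of N are used: 1310 (the stated requirement), 1440 (2400 less 40%) and 1680 (2400 less 30%).

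**4. Probability of passing, and mean size when passed.** Let d be the true interaction, s its SE, a = 1.96 − d/s and b = −1.96 − d/s. On normal theory:
- P(p<0.05) = 1 − Φ(a) + Φ(b)
- Mean |estimate| given p<0.05 = {d[1 − Φ(a)] + sφ(a) − dΦ(b) + sφ(b)} / P

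The interaction sizes of 2.5 min (half the target effect) and 5 min are assumptions.

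| N | SE (min) | Smallest significant estimate (min) | d=2.5: passes | d=2.5: mean shown (inflation) | d=5: passes | d=5: inflation |
|---|---|---|---|---|---|---|
| 1310 | 1.56 | 3.06 | 36% | 4.1 min (1.65) | 89% | 1.06 |
| 1440 | 1.49 | 2.92 | 39% | 4.0 min (1.59) | 92% | 1.05 |
| 1680 | 1.38 | 2.70 | 44% | 3.7 min (1.49) | 95% | 1.03 |

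With an even split, each subgroup effect is the average effect plus or minus half the interaction. At N=1310 an excess of 4.1 − 2.5 = 1.6 min therefore moves each of the two subgroup effects about 0.8 min from the truth, in opposite directions.

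**5. Range under other assumptions, d=2.5 min.**
- 20:80 split, N=1310: SE 1.95, passes 25%, inflation 1.99.
- Moderator varying only between schools (worst case), N=1310: SE 3.08, passes 13%, inflation 3.0.
- 50:50 split with no loss, N=2400: SE 1.15, passes 58%, inflation 1.31.

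**6. No true moderation.** Chance that at least one of five independent tests passes: 1 − 0.95⁵ = 0.226. On average 5 × 0.05 = 0.25 moderators pass. A null interaction that passes shows a mean absolute size of about 3.65 min at N=1310 (50:50), roughly three quarters of the 5 min target.

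**The case against.** Requiring an interaction test before interpreting subgroups is a recognised guard against spurious claims. Naming five moderators in advance and limiting them to the primary outcome is good practice. Both points stand, and the interaction tests should stay. They support using the test to guide interpretation. They do not require that the subgroup estimates be withheld.

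A reader might infer that non-significant moderators will yield no estimate at all. The text does not support that. All five interactions are tested, and fitting each model gives a coefficient and standard error. Only the within-subgroup effects and their CIs are made conditional.

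A reader might also infer that whatever is reported must be exaggerated or due to chance. That is too strong: a true 5 min student-level interaction with an even split would pass 89%–95% of the time at the sample sizes above, with 3%–6% inflation.

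Multiplicity handling and table layout for secondary analyses may sit in an analysis plan that is not shown, so their absence is not held against the article. The condition itself is different. It is a stated rule, and an analysis plan that follows the article would carry it forward.

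**Conclusion.** The point holds in limited form. Within-subgroup effects are selected on significance. For interactions of about half the target effect, the interaction shown would be overstated about 1.5- to 1.65-fold at the expected sample sizes with an even split, and about 1.3- to 3-fold across the wider range examined. A moderator that does not pass has no planned subgroup effect or CI, which leaves similar effects and an imprecise test indistinguishable.

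These sizes rest on assumed interaction magnitudes and subgroup shares, on normal theory, and on school effects cancelling for student-level moderators. The 23% figure also assumes independent tests. The primary estimate and the sample size are not affected, so this is a matter for a stated secondary objective.

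**What to change.** Keep the five prespecified interaction tests and remove the p<0.05 condition. For all five moderators, report the interaction estimate with 95% CI and the effect with 95% CI in each subgroup, whatever the p value. Label the results exploratory and state that five tests were made.

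Reporting everything removes the selection. It does not lower the 23% chance of at least one nominally significant result; the label and the stated number of tests only make that visible.

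The cost is one changed sentence and one extra table or forest plot, with no new data. There is some added risk that readers over-interpret differences between subgroups, which the exploratory label and the interaction test beside each pair of estimates limit.

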#### Qualitative analyses

Focus groups and interviews will be audio recorded, transcribed verbatim and made anonymous. Data will be analysed using thematic analysis following a six-phase model,^59^ facilitated by QSR NVivo. Coding will be inductive, incorporating emerging themes as well as topics presented a priori in the interview guide. Initial analyses will inform future data collection and analysis. Interim themes will be discussed by the research team to reach consensus.

#### Cost-effectiveness analyses

Cost-effectiveness analyses will follow standardised protocols.^60^ The main economic outcome will be the incremental cost-effectiveness ratio, expressed as incremental costs per incremental change in physical activity (MVPA) and per QALY gained (based on CHU-9D) for the trial period (including follow-up). Data collected will include intervention time, travel, expenses, resource use and study-specific costs. In addition, if GoActive increases physical activity, this should reduce adult chronic disease via changes in weight or BMI, and blood glucose. To establish whether GoActive could increase length and/or quality of life and at what cost, it is not practical to conduct lifetime follow-up, therefore we propose adjusting an existing decision-analytic model to estimate the impact of physical activity on disease risk, quality-adjusted life expectancy (QALY) and cost to the NHS. The modelled analysis will therefore be from a public sector perspective (schools/local authority and NHS).

### Further analyses

Further research questions can be addressed using the cohort data, including (but not limited to) assessment of the predictors of activity maintenance, and the longitudinal association between physical activity/sedentary behaviour and (1) academic performance, (2) shyness and sociability and (3) friendship quality. All proposed analyses will be approved by the project group, and authorship of manuscripts will be informed by recommended guidelines.^61^

### Ethics and dissemination

Ethical approval for the conduct of the study was gained from the Cambridge Psychology Research Ethics Committee, who previously provided ethical approval for the development, feasibility and pilot studies following similar procedures.^22 26^

If successful, it would be appropriate to disseminate this programme to schools and councils across the UK (in addition to peer-reviewed publications). Towards the end of the project, a deliberative dialogue workshop will be held with key stakeholders including students, parents, teachers, school governors and representatives from local/national government. This final workshop will focus on plans for dissemination of results and will include discussion of the process of programme adaptation to a diverse range of secondary schools and further ways of ensuring long-term appeal for adolescents. We anticipate that dissemination could be facilitated through the study website, hosting intervention materials (including videos) and study information.

Given the lack of rigorously evaluated interventions, the results of a CRCT of the effectiveness and cost-effectiveness of GoActive are expected to add substantially to the limited evidence on adolescent physical activity promotion. This study will include an objective, wrist-worn measure of physical activity, aligning with contemporary population surveillance studies^62–64^ and ensuring greater protocol compliance for enhanced data retention and quality.^32 34 35^ Achieving sustained health behaviour change is an established priority,^10^ and so the inclusion of medium-term to long-term follow-up of participants will enable conclusions regarding the trajectories of change (in particular, whether any initial behaviour change is maintained). It will also form one of the largest cohorts in the field of adolescent physical activity promotion, providing many opportunities for secondary data analysis, in addition to testing causal pathways of effect and examining cost-effectiveness. Irrespective of study outcome, the evaluation of the GoActive intervention to increase physical activity in adolescents has the potential for significant academic impact.
